## Abstract

**Background:**

Dystonia is one of the most common forms of movement disorder, caused by the co-contraction of antagonistic muscles, leading to abnormal postures and considerable disability. Non-motor symptoms, notably psychiatric disorders, are well recognised comorbid features of the disorder. However, there is no standardised model for the management of these symptoms in dystonia, with them frequently going undiagnosed and untreated. An internet-based cognitive behavioural therapy programme may provide a future model of care that also maximises available resources.

**Methods:**

This study represents a two-armed randomised feasibility trail, aiming to recruit a total of 20 participants with a diagnosis of adult-onset primary focal cervical dystonia. Participants will be recruited from the Global Myoclonus Dystonia Registry and Dystonia Non-Motor Symptom Study (conducted at Cardiff University) based on presence of moderate symptoms of anxiety/depression as indicated by standardised questionnaires. All participants will undergo assessment at baseline, 3 and 6 months, with this including questionnaires for assessment of non-motor symptoms and clinical assessment of motor symptom severity. Participants will be randomised to either the control (*n* = 10) or treatment (*n* = 10) groups. The treatment group will be asked to complete one session of the online CBT program a week, for 8 weeks. The primary outcome measure will be the engagement of participants with the programme, with secondary outcomes of non-motor and motor symptom scores.

**Discussion:**

Promising results have been shown using face-to-face cognitive behavioural therapy to reduce levels of anxiety and depression in individuals with a diagnosis of dystonia. However, no studies to date have sought to determine the feasibility of an internet-delivered cognitive behavioural therapy programme. A number of effective internet-based programmes have been developed that combat anxiety and depression in the general population, suggesting the potential for its effectiveness in cervical dystonia patients. Success with this study would significantly impact the clinical care delivery for patients with cervical dystonia, as well as widening potential access to effective treatment.

**Trial registration:**

This feasibility trial has been registered with Health and Care Research Wales Research Directory. Trial registration number 44245. Date of registration: 21 November 2019. https://www.healthandcareresearch.gov.wales/research-studies-in-wales/

## Background

### Background and rationale

Dystonia is the third most common form of movement disorder, with an estimated prevalence of 1/900 (dystonia.org.uk). It involves co-contraction of antagonistic muscle groups leading to abnormal postures and movements, causing considerable disability. As a result, the disorder is associated with significant social, educational and health economic implications. There is also increasing recognition that non-motor symptoms form an important part of the disorder [1, 2]. A consistent psychiatric phenotype has been demonstrated across a number of cohorts, with up to 65.9% of individuals affected with symptoms including major depressive disorder and anxiety-related disorders [3–5]. Psychiatric symptoms, in particular anxiety and depression, have been shown to have a significant impact on the quality of life of individuals with cervical dystonia, and in some cases a larger impact on their physical quality of life than the severity of the dystonia itself [6–8].

Comorbid psychiatric symptoms in dystonia are frequently undiagnosed and largely untreated. There is no standardised model for the management of these symptoms, and for those who do receive treatment, this is often pharmacological, with many of the currently available treatments adversely affecting the underlying movement disorder [9]. Non-pharmacological interventions, such as psychological therapies, represent a potentially beneficial form of treatment, allowing primary management of the psychiatric symptoms while also benefitting overall motor function. Cognitive behavioural therapy (CBT) is a well-recognised psychotherapeutic approach that uses goal-orientated, systematic procedures to address cognitive processes and maladaptive behaviours, beliefs and emotions.

CBT has been shown to be particularly effective in the management of the psychiatric symptoms frequently observed in cervical dystonia [10, 11], with a recent feasibility study demonstrating the ability for face-to-face CBT combined with mindfulness to substantially reduce depression and anxiety scores using standardised questionnaires [12]. Unfortunately, timely access to face-to-face psychological therapy is often limited due to cost, waiting times, a shortage of suitably qualified therapists and the stigma associated with psychological therapy. As a result, a number of online, guided self-help CBT programmes have been developed, validated and shown to be successful in the management of anxiety and depression [13–15].

This study aims to demonstrate the feasibility of a validated online guided, self-help CBT programme in the management of non-motor and motor symptoms for patients with cervical dystonia. We believe this has the potential to provide a platform for a fully integrated, and cost-effective, model of care that could be implemented alongside currently available medical management, widening access to effective treatment and maximising the use of healthcare resources.

### Aims and objectives

This study is a two-arm randomised control feasibility study with the specific aim to determine the feasibility of a guided, internet-based self-help CBT programme in the management of psychiatric symptoms in patients with cervical dystonia. A secondary objective of this study is to explore the difference in non-motor and motor symptoms in patients with cervical dystonia that have completed an online CBT programme in comparison to those receiving routine clinical treatment of their motor symptoms alone.

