#### Secondary objectives

(i)To explore if an online, self-guided CBT programme can reduce depression and anxiety levels in individuals with cervical dystonia.(ii)To explore if improvement to anxiety and depression levels subsequent to the CBT program also have an impact on the motor symptoms observed in those with cervical dystonia.

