### Study design

This study is a two-arm randomised feasibility study of a guided, internet-based self-help CBT programme for people with cervical dystonia, which also have elevated levels of depression and/or anxiety determined through the use of three clinically validated standardised questionnaires (Beck’s Depression Inventory, Health Anxiety Inventory, and Modified Mini Screen). All participants will undergo baseline assessments and assessments at 3 and 6 months that will take place either in the participants’ home or at our research clinic, dependent on the preference of the participant. These assessments will include a number of questionnaires relating to non-motor symptoms, including psychiatric symptoms, sleep disturbance and pain, as well as overall quality of life. A videotaped, standardised clinical examination will also be undertaken for assessment of their motor symptoms. This will allow for blinded rating of motor symptoms by two movement disorder experts. Those allocated to the control group will continue to receive only their routine clinical care for treatment of their motor symptoms, namely 3-monthly neurotoxin injections. Those allocated to the intervention will receive support setting up their account for the online CBT programme and receive guidance on how the programme works. The study schema is illustrated in Fig. 1.

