## Methods

### Participants, interventions and outcomes

#### Study setting

Participants will be recruited from the Global Myoclonus Dystonia Registry and Dystonia Non-Motor Symptom Study (REC 18/WM/0031 IRAS project ID: 236219). Only individuals that have consented to be contacted about future studies will be contacted. Participants meeting the inclusion criteria for this study will be sent a study flyer inviting them to enquire further if they are interested in taking part in the research. A participant information sheet (PIS) will then be sent, and the potential participant will be invited to make an appointment at their convenience for their baseline assessment. Baseline assessment will include evaluation of the participant’s motor and non-motor symptoms as well as a standardised clinical examination (Table 1; Fig. 1). Baseline demographic information will already have been collected as part of the dystonia non-motor study (Fig. 1). This appointment will also include randomisation to either the treatment or the control arm.

**Table 1 Tab1:** Study outcome assessments

Assessment	Description	Approximate duration	Type of data collected
*Psychiatric*			
Beck’s Depression Inventory	A 21-item questionnaire to identify mild mood disturbances, borderline clinical depression, moderate depression, severe depression or extreme depression. Freely available	2 min	Quantifiable
Hamilton Depression Rating Scale	A widely used and well-validated tool for measuring a patient’s depression, identifying mild, moderate, severe and very severe levels of depression	15–20 min	Quantifiable
Generalised Anxiety Disorder-7	A 7-item questionnaire to identify mild, moderate, or severe levels of anxiety. Freely available	< 1 min	Quantifiable
Hamilton Anxiety Rating Scale	A widely used and well-validated tool for measuring anxiety able to indicate mild, moderate, and severe levels of anxiety	15–20 min	Quantifiable
Mini International Neuropsychiatric Interview	An interview that covers a wide range of neuropsychiatric disorders including depression, panic disorders, anxiety, obsessive-compulsive disorder (OCD) and post-traumatic stress disorder (PTSD)	15–20 min	Yes/no
*Sleep*			
Sleep Disorders Questionnaire	A 16-item questionnaire that assesses insomnia, psychiatric disorders, circadian rhythm disorder, movement disorders and parasomnias. Freely available	1.5 min	Likert scale

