### Details of intervention

The online CBT platform will be hosted by SilverCloud Health Ltd (www.silvercloudhealth.com). Participants will be directed to the study-specific website where they will enter a unique identifying code and be provided with a link to the ‘Space for Anxiety and Depression’ module of the Silver Cloud website. This is a fully validated online CBT programme, delivering evidence-based content and adapted to integrate and deliver to NICE standards of care [16, 17]. The programme content is modular (Table 3), with participants encouraged to complete one module a week (lasting 30–40 min), over 8 weeks. Participant accounts will be linked to researcher accounts to enable remote monitoring and provide a record of timing and frequency of login by the participant. Participants will also receive weekly reminders to encourage them to log into the programme. Also available as part of the programme will be a number of optional tools (Table 3) that participants are free to engage with to any degree they wish.

**Table 3 Tab3:** Description of the online SilverCloud content including description of the core modules and additional available tools

Main module content	Title	Description of content
Module 1	Welcome to Silver Cloud	An introduction to the programme and how to make the most of the available resources.
Module 2	Getting Started	Demonstrates the basics of CBT and depression and anxiety. Introduces some of the key ideas of the programme.
Module 3	Understanding Feelings	This module takes a closer look at moods and emotions enabling the participant to explore different aspects of emotions, physical reactions and to see how they’re connected.
Module 4	Boosting Behaviour	Addresses how doing things a little differently can help to improve mood.
Module 5	Spotting Thoughts	Looks at the impact of unhelpful automatic thinking in relation to mood. Additional help to tune into thoughts and recognise any common thinking errors.
Module 6	Challenging Thoughts	This module takes the next step in helping to tackle distorted or overly negative thinking patterns that may impact mood.
Module 7	Managing Worry	Introduces the role of worry in anxiety, teaching techniques in how to cope with and manage worry more effectively.
Module 8	Bringing it all Together	Brings together all of the skills developed, and ideas gathered so far.
Additional tools		
Personal Journal	Allows participants to document entries relating to their experiences in relation to the modules.	

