### Outcome assessments

As this study aims to determine feasibility of this approach to treatment, the outcome measures selected for inclusion have been selected to help inform future, larger trials. Baseline and outcome assessments will be completed during the study (Table 1). This extended range of non-motor and motor assessments (Table 1) will be completed either during home visits or when the participant attends the research clinic. Prior to statistical analysis, the videotaped clinical examinations of motor symptoms for each participant will be independently rated by two movement disorder experts blinded to the randomisation, with these scores included in the final analysis. To assess the feasibility of the internet-based CBT programme, we will also collect data on the number of logins to the internet-based CBT programme using the SilverCloud website. We will collect information on the number of logins and the number of modules completed at 8 weeks, 3 months and 6 months, along with the proportion of participants that used the additional resources included with the programme. We will also determine how many participants complete the 3- and 6-month follow-up and, at these appointments we will ask if they found the programme useful and if it was something that they would continue to go back to.

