#### Trial arms

Following randomisation, participants will be given verbal instructions related to their allocated trial arm by a member of the trial team. Participants randomised to the treatment arm will undergo an introduction to the online, guided, internet-based CBT programme by the trial team before being asked to complete weekly 30–40-min sessions of the programme over the following weeks. Participants will receive weekly prompts, either by text, telephone or email, during the course of the programme to remind and encourage them to log in. Aside from this, the participants will be able to choose their degree of engagement with the programme. Participants will undergo follow-up assessments, following the same structure as the baseline assessment at 3 and 6 months following their initial appointment to determine any longer-term effects of the online CBT programme. Participants randomised to the control group will undergo follow-up assessments at 3 and 6 months following their baseline assessments. All participants will continue to receive their routine injectable neurotoxin treatment for management of their motor symptoms throughout.

Participants in both trial arms will be directed to resources for urgent help and support if required throughout the study. This will include contact details for the trial team during regular working hours and the contact details of a national support helpline. Participants will be requested to attend their local A&E department if the support required is deemed urgent and severe. The participant’s general practitioner (GP) will also be informed of any symptom deterioration by the study team.

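### As worded, the exploratory secondary objective compares CBT completers with all controls, a contrast that randomisation does not protect

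*Protocol article*

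**What the plan says.** Under Aims and objectives, the secondary objective sets out the symptom comparison, motor and non-motor alike, as follows: "patients with cervical dystonia that have completed an online CBT programme in comparison to those receiving routine clinical treatment of their motor symptoms alone". Study design identifies the comparator by allocation: "Those allocated to the control group will continue to receive only their routine clinical care for treatment of their motor symptoms".

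On timing, Study setting says of the baseline visit: "This appointment will also include randomisation to either the treatment or the control arm". The programme follows, with "participants encouraged to complete one module a week (lasting 30–40 min), over 8 weeks" (Details of intervention). Apart from weekly prompts, "the participants will be able to choose their degree of engagement with the programme" (Trial arms). Adherence is itself a feasibility measure, recorded as "the number of modules completed at 8 weeks, 3 months and 6 months" (Outcome assessments).

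Secondary objective (i) asks whether the programme can reduce depression and anxiety in people with cervical dystonia. It does not mention completion. Statistical methods names Student's t test or the Wilcoxon rank sum test for scores, and chi-squared or Fisher's exact test for categorical variables. It does not say which groups or which participants enter those tests.

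**The concern.** Randomisation makes the two arms comparable as allocated. It does not make a subset of one arm, picked by what its members did afterwards, comparable with the whole of the other. People who finish eight weekly modules may differ in motivation, severity or prognosis from those who stop. The Discussion itself lists lack of time, of IT skills and of motivation to change among the barriers to engagement. Controls who would have stopped cannot be identified and removed, so a difference between completers and all controls mixes that selection with any effect of CBT.

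Outcome assessments says the measures were chosen to inform later, larger trials. An effect estimate drawn from completers could therefore carry its selection into the planning of such a trial. The Aims sentence matters because it is the only place in the article that states who is compared with whom on symptoms.

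**Working it through.** **Reading the text.** Four facts settle what the sentence means if followed literally.

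1. Allocation is fixed at the baseline visit (Study setting).
2. Completion builds up over the following 8 weeks (Details of intervention), so it is a post-randomisation event.
3. The degree of engagement is the participant's choice (Trial arms), so completion is self-selected.
4. The comparator is everyone allocated to control (Study design), with no matching condition.

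Modules are counted at three time points and the article gives no threshold for having completed, so the wording does not identify a single set of completers either.

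**Size, as an illustration.** The plan gives no effect size, SD or completion rate, so there is no figure of its own to reproduce. Inputs:

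- From Sample size: 10 participants per arm.
- Assumed: completion fraction p = 0.5, 0.6 or 0.8.
- Assumed: correlation rho = 0.3 or 0.5 between a normally distributed propensity to complete and the outcome.
- Assumed: no CBT effect, and outcome SD of 1 in both arms.

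If the fraction p with the highest propensity completes, the mean outcome of completers differs from that of controls by

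bias = rho × φ(z) / p, where z is the (1 − p) quantile of the standard normal and φ its density.

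- p = 0.5: φ(0)/0.5 = 0.399/0.5 = 0.798. Times 0.3 = 0.239 SD; times 0.5 = 0.399 SD.
- p = 0.6: φ(−0.253)/0.6 = 0.386/0.6 = 0.644. Times 0.3 = 0.193 SD; times 0.5 = 0.322 SD.
- p = 0.8: φ(−0.842)/0.8 = 0.280/0.8 = 0.350. Times 0.3 = 0.105 SD; times 0.5 = 0.175 SD.

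Simulation with 10 per arm agrees with the formula. Over these six settings, the type I error of a two-sided 5% t test of completers against all controls is about 5.5% to 9.9%. The bias is zero if rho = 0 or if everyone completes. A negative rho reverses its sign, which would happen if, say, the more distressed participants were the ones who persisted.

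**Precision.** In SD units the standard error of the difference is √(1/10 + 1/n), where n is the number analysed in the CBT arm.

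- n = 10: 0.447
- n = 8: 0.474
- n = 6: 0.516
- n = 5: 0.548

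Dropping non-completers therefore costs precision as well. With all 10 against 10 compared as randomised, and outcome data complete, the selection bias is zero for any p and rho.

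**The case against.** The strongest reply is that one summary sentence is being read as an analysis population. Secondary objective (i) has no completion condition. Statistical methods restricts nothing to completers and describes baseline by trial arm. Study design and Trial arms define the groups by allocation, and every participant is assessed at 3 and 6 months. On that reading, having completed the programme loosely means having been given it. The analysis set could also be fixed in a statistical analysis plan that is not shown.

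Much of this stands. A reader might infer that the trial has planned a completers-only analysis; the article does not say so, and the absence of a stated analysis set is not in itself a fault in a condensed article. What remains is a sentence that is present and says the wrong thing. It conflicts with objective (i), and a plan written from it would inherit a non-randomised contrast.

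The size argument also has force. The completion rates and correlations are assumed. Even the largest bias, 0.40 SD, is below the matching standard error of 0.548 SD. In a trial this small, chance will usually outweigh the selection. Selection, however, is a systematic error that the reported interval would not show.

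A reader might also take secondary objective (ii), "To explore if improvement to anxiety and depression levels subsequent to the CBT program also have an impact on the motor symptoms", as a second comparison conditioned on a post-randomisation event. It is not. It asks an exploratory question about the link between mood and motor change and restricts no comparison to those who improved. How that link is modelled is a matter for the analysis plan.

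**Conclusion.** The concern holds for the wording of the objective. Followed as written, the secondary comparison sets a self-selected, post-randomisation subset of the CBT arm against the whole control arm. It also conflicts with secondary objective (i). With no CBT effect, the resulting bias would be about 0.10 to 0.40 SD, on the assumptions of 50% to 80% completion and a correlation of 0.3 to 0.5 between propensity to complete and outcome. None of these inputs comes from the documents.

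Severity is minor to moderate. It might be tempting to conclude that the trial's results are compromised, but the documents do not support that. The primary outcome is engagement and is untouched, both secondary aims are exploratory, no decision rule hangs on the clinical comparison, and the data for an as-randomised comparison will be collected in any case.

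**What to change.** 1. In Aims and objectives, reword the secondary objective so that it compares all participants allocated to the online CBT programme with all allocated to control, whatever number of modules they completed. This brings it into line with secondary objective (i).
2. In Statistical methods, add one sentence: the t test or Wilcoxon and the chi-squared or Fisher comparisons of symptom scores use the groups as randomised.
3. Keep any presentation of outcome by modules completed as a descriptive table within the CBT arm, labelled as non-randomised, with completion defined by a stated number of modules and time point.

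The cost is one reworded sentence, one added sentence and, if wanted, one descriptive table from data already planned. No extra participants, visits or measurements are needed.
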